## Abstract

**Background:**

Australia has a comparatively high incidence of colorectal (bowel) cancer; however, population screening uptake using faecal occult blood test (FOBT) remains low. This study will determine the impact on screening participation of a novel, Internet-based Personalised Decision Support (PDS) package. The PDS is designed to measure attitudes and cognitive concerns and provide people with individually tailored information, in real time, that will assist them with making a decision to screen. The hypothesis is that exposure to (tailored) PDS will result in greater participation in screening than participation following exposure to non-tailored PDS or resulting from the current non-tailored, paper-based approach.

**Methods/design:**

A randomised parallel trial comprising three arms will be conducted. Men and women aged 50-74 years (*N *= 3240) will be recruited. They must have access to the Internet; have not had an FOBT within the previous 12 months, or sigmoidoscopy or colonoscopy within the previous 5 years; have had no clinical diagnosis of bowel cancer. Groups 1 and 2 (PDS arms) will access a website and complete a baseline survey measuring decision-to-screen stage, attitudes and cognitive concerns and will receive immediate feedback; Group 1 will receive information 'tailored' to their responses in the baseline survey and group 2 will received 'non-tailored' bowel cancer information. Respondents in both groups will subsequently receive an FOBT kit. Group 3 (usual practice arm) will complete a paper-based version of the baseline survey and respondents will subsequently receive 'non-tailored' paper-based bowel cancer information with accompanying FOBT kit. Following despatch of FOBTs, all respondents will be requested to complete an endpoint survey. Main outcome measures are (1) completion of FOBT and (2) change in decision-to-screen stage. Secondary outcomes include satisfaction with decision and change in attitudinal scores from baseline to endpoint. Analyses will be performed using Chi-square tests, analysis of variance and log binomial generalized linear models as appropriate.

**Discussion:**

It is necessary to restrict participants to Internet users to provide an appropriately controlled evaluation of PDS. Once efficacy of the approach has been established, it will be important to evaluate effectiveness in the wider at-risk population, and to identify barriers to its implementation in those settings.

**Trial registration:**

Australian New Zealand Clinical Trials Registry ACTRN12610000095066

## Background

In Australia, the risk of being diagnosed with colorectal cancer (CRC) by the age of 85 years is 1 in 10 for males and 1 in 14 for females, with the risk increasing sharply from the age of 45 years [1]. In 2006, CRC accounted for 10% of all invasive cancer-related deaths, second only to lung cancer [2]. Despite evidence from randomised clinical trials that both biennial and annual screening using faecal occult blood testing reduces CRC mortality [3-5] and incidence [6], the participation rate remains low. Since 2007 the Australian government-funded National Bowel Cancer Screening Program (NBCSP) has been operational and now provides people turning 50, 55 and 65 years with a free Faecal Occult Blood Test (FOBT) kit. This home-based test involves sending a stool sample to a laboratory to be analysed for occult blood, ideally followed by colonoscopy for those with a positive result. The 2008 participation rate was 39% of the eligible population [1], with uptake varying between sexes (42% for females compared to 36% for males). These suboptimal rates highlight the public health challenge to optimise participation rates using publicly delivered rather than clinician-based interventions.

An understanding of the variables that encourage people to participate in CRC screening using FOBT is important for a number of reasons. Participation rate is the critical determinant of population efficacy of screening as it improves outcomes independent of screening technology. Early detection and treatment of precancerous lesions and adenomas results in a significantly higher survival rate than if treatment is delayed until physical symptoms of the conditions are evident [4]. Moreover, the cost effectiveness of FOBT screening is expected to increase as greater participation and earlier detection of CRC reduces treatment costs and improves longer-term survival rates [7].

Poor participation in screening can be attributed to several factors including a poor understanding of cancer and cancer risk [8], insufficient knowledge of CRC and the value of screening [9,10] and a perception of the screening process as distasteful or embarrassing [11,12]. Decision aids have been developed to overcome some of the problems associated with poor participation in cancer prevention programs including participation in CRC screening. Their purpose is to assist the decision making of people facing health treatments or screening decisions through increasing knowledge of and awareness about personal risk and response alternatives. Screening aids have been shown to improve knowledge, reduce decisional conflict and stimulate individuals to be more active in decision making without increasing their anxiety [13,14]. Furthermore, a meta-analysis of the effectiveness of these aids confirms their utility for improving knowledge of cancer screening by comparison to usual practice [15]. The utility of these aids is likely to be affected by several factors including the theoretical framework underpinning the aid, the format of the decision aid and the nature and presentation of the information.

### Theoretical framework

Two classes of behavioural theory hold particular relevance to the development of decision aids designed to enhance screening participation. These are described as "continuum" and "stage" theories [16]. Continuum theories focus on the exploration of psychosocial predictors of intention to screen; a recent variant, the Preventive Health Model (PHM), draws from other theoretical models including the Health Belief Model [17]. The PHM indicates that individual differences in preparedness to screen for CRC can be attributed to scores on five factors: salience and coherence (the extent to which performing CRC screening is consistent with beliefs about how to protect and maintain health); cancer worries (concerns about the consequences of CRC); response efficacy (beliefs that undertaking CRC screening will be effective in reducing disease threat); social influence (beliefs about, and desire to comply with the attitudes of key others to CRC screening); and perceived susceptibility (subjective personal risk for developing CRC). These constructs have been validated in the U.S. [18,19] and Australia [20]. It has been argued that the PHM is enhanced when utilised with a "stage" theory such as the Precaution Adoption Process Model (PAPM) [21] which deconstructs behavioural intention and posits that individuals are more likely to respond to interventions aimed at their stage of readiness to engage in screening. The PAPM describes people as being at one of seven stages: unaware of the issue, heard of the issue but unconcerned, considering action, decided against a behaviour, decided to act, acting and lastly, maintaining the behaviour over time. Myers and colleagues have demonstrated that groups of people at a specific stage of thinking about colorectal cancer screening can be distinguished from people at a higher level in terms of their responses to the variables included in the PHM [22]. For example, for those people who have "never heard of" FOBT (unaware of the issue), messages which emphasise the PHM factors of salience and coherence and perceived susceptibility are more likely to move them toward a decision to screen, whereas messages focussing on perceived susceptibility and self efficacy are more likely to resonate with those who have "decided against" screening and encourage them toward screening.

### CRC screening decision aid format and the presentation of information

The PAPM and PHM models provide the basis upon which to develop an understanding of the cognitive frame of reference that underlies an individual's decision-making around CRC screening. Research suggests that the effectiveness of decision aids is enhanced when the information provided is tailored to the needs of the individual; the communications are consistently better remembered and perceived as being more relevant than non-tailored materials [23]. Tailoring messages according to current decision stage (PAPM), and current responses on the full range of psychosocial drivers measured in models like the PHM, should enhance participation, maximise a person's satisfaction with their decision, and minimise any feelings of anxiety or dissonance ("decisional conflict").

Paper-based delivery of tailored messages has improved screening uptake [24] but the feasibility of this approach, if implemented on a large scale, has yet to be established. A meta-analysis comparing web-based and non-web-based informational interventions showed enhanced outcomes among individuals using web-based interventions, particularly in the areas of knowledge and targeted behaviour change [25]. The potential advantages of web-based delivery over traditional paper methods include the ability to present information to the reader in a way that is more easily navigable than on paper; the capacity to use context to enhance relevance through the process of tailoring on key variables; and the ability to provide instantaneous enactment of the decision reached, thereby avoiding the difficulties that are attached to procrastination (for example, screening tests could be ordered instantly online or an appointment made with a doctor via email). Thus, there is a need to test whether electronic delivery can achieve similar or improved uptake rates compared to paper-based delivery, particularly within a community setting.

A functional Internet-based Personalised Decision Support system (PDS) developed by the Commonwealth Scientific and Industrial Research Organisation (CSIRO) Preventative Health Flagship is available for this study. It is an interactive application that collects user information in real-time and delivers instantaneous, personalised messages aimed at moving individuals through the decision stages relevant to CRC screening. An extensive User Model drives a series of algorithms that underlie an educational message library. These algorithms have been developed to ensure that messages delivered to an individual are united with natural language so that they can be read in a coherent, logical manner. After log-in, individuals complete a questionnaire that incorporates PAPM and PHM variables. Items are rated on a 5-point Likert scale from 'strongly disagree' to 'strongly agree'. The computer program processes these data to determine the individualised content to be delivered following completion of the questionnaire. The resulting web interface consists of tailored, personalised messages that address relevant knowledge deficits and reinforce perceptions when favourable to screening, or motivate people to change perceptions when unfavourable. For example, a library of messages has been created to address response efficacy, a factor which relates strongly to those who are "not considering" FOBT screening. The response efficacy statement reads: "When colorectal polyps are found and removed, colorectal cancer can be prevented". Participants who respond "disagree" receive a personalised 'motivating' message reading; "[Participant's name], *you don't believe that colon cancer screening is effective. In fact, it's very effective ...*" Participants who respond '"agree" would receive a 'reinforcing' message: "*You've told us that you believe colon cancer screening is effective. You're right ...*" Messages are also presented in a specific order so that messages relating to PHM factors which are most strongly associated with an individual's current decision stage [22] are presented first with the aim of moving people through stages of screening awareness and pre-screening contemplation to a decision to participate.

In conclusion, communicating the necessity for CRC screening and the effectiveness of screening tests available to the target population is a clearly demonstrated need. Tailored decision support, delivered via the Internet, holds the prospect of improving participation rates and thereby health outcomes into the future.

## Methods/Design

### Study Aims

The primary aims of the study are to test whether (1) an Internet-based, Personalised Decision Support package (PDS) that delivers personalised information, tailored according to preventive health variables and current decision stage for screening enhances FOBT participation when compared to a non-tailored PDS package and the current paper-based approach; and (2) whether tailored PDS moves individuals to a higher decision stage for screening compared with the other interventions.

### Study design and setting

This study is a parallel group, randomised trial where a randomly-selected, national sample of 3240 men and women aged 50 to 74 years who are known to have Internet access are randomised to a tailored or non-tailored PDS, or a non-tailored, paper-based approach (usual practice). Only one member from each household will be recruited to avoid cross-contamination of the groups. The trial design flowchart, with estimated attrition rates, is shown in Figure 1.

**Figure 1 F1:**
[figure not shown]
**Trial design flow chart and estimated attrition rates**.

#### Ethical considerations

Full ethical approval has been obtained from the CSIRO Human Research Ethics Committee.

### Identification of eligible participants

We will approach a randomly selected, national mainland Australian sample of *N *= 18,000 urban dwelling, men and women aged 50-74 years identified from the electoral roll. The sample will be stratified according to population density at the Australian State level. Rural areas and Tasmania will not be included because the former will have added constraints associated with potential difficulties in accessing gastroenterological services and the latter has a population too small to allow for appropriate stratification. Potential participants will be approached via a posted Eligibility Questionnaire (EQ) and information sheet outlining the nature and requirements of the study and asking them to address the inclusion and exclusion criteria if they are interested in participating. A pre-paid return envelope will be enclosed for return of the documents. There will be an opportunity for people to opt out at this stage.

#### Determining eligibility for the study

Potential participants will be selected from those who return the EQ and who are eligible based on criteria shown in Additional File 1.

#### Randomisation

Those who have indicated, by return of the completed EQ, that they have read the study information, are eligible and willing to participate in the study will be randomly assigned to one of three arms (Figure 1). Block randomisation using random block size will be utilised, and stratification will be performed to ensure that the numbers of participants receiving each intervention are closely balanced within each Australian State.

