Participants in each of the two PDS arms will be required to access the PDS web site and log in with a unique user name and ID provided by the researchers. Once logged on, participants in both arms will complete a Baseline Survey (BS) that will collect demographic data, PAPM decision stage and measure PHM variables. Participants in the *Tailored PDS *arm will receive appropriately motivating or reinforcing messages tailored to their responses to the BS variables. In addition they will be able to access an electronic version of the NBCSP's consumer information booklet [26]. This provides information about the NBCSP, including information on bowel cancer, screening, and completing the FOBT kit. In the *non-tailored PDS *arm, participants will not receive any tailored messages upon completion of the BS but they will be able to access the NBCSP consumer information booklet. In the *paper-based *usual practice arm, the BS only (without an accompanying consumer information booklet) will be offered by mail. At that stage, all participants will be informed that they will receive an FOBT kit approximately 2 weeks after completion of the BS. This information will equate to the 'pre-notification' process employed in the NBCSP.

All participants who have not opted out of the trial at the BS phase and have completed a BS will receive a commonly used FOBT kit of the immunochemical type (Faecal Immunochemical Test, FIT) that does not require dietary or drug restrictions, and an invitation to screen. In the usual practice arm, the offer will consist of a mailed, personalised (by name and address) invitation to screen and will include printed educational material in the form of the NBCSP consumer information booklet. The offer to PDS participants will parallel that of the usual practice arm, with the distinction that the printed educational material will not be provided but both groups will be reminded that they may return to the PDS using their supplied username and password to re-visit messages (tailored arm) and the electronic version of the NBCSP consumer information booklet. A reminder will be sent 6 weeks after despatch of FOBT to those who have not returned their kit.

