### Sample size considerations

Randomisation of 3240 participants (1080 in each arm) takes into consideration predicted attrition of 50% at BS survey phase, followed by screening offers being distributed to 1620 survey respondents (540 in each arm). This permits detection of differential FOBT uptake of at least 10% between two groups (e.g., 40% vs 50%) with 80% power and alpha of 0.05. To recruit this number of participants, an initial sample of 18,000 needs to be approached, given our estimated attrition rates throughout the study (Figure 1).

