## Discussion

The study aims to test the *efficacy *of the intervention in participants where the intervention and the screening process seem feasible. We acknowledge that requiring participants to have access to the Internet may raise concerns about health equity. However, it is necessary to restrict participants to Internet users to provide an appropriately controlled evaluation of PDS. Moreover, we do not consider this restriction will represent an undesirable degree of selection bias as the results of an earlier study we conducted found that more than half the population over 50 years in South Australia has access to the Internet at some location [29]. Likewise, participation is limited to those living in urban postcode regions. This is because those who have a positive FOBT result will be more likely to achieve speedy access to gastroenterological services [30] and incur fewer personal costs and difficulties [31]. Restriction of study participants to those living in urban areas will avoid confounding of the results by service accessibility issues. Once efficacy of the approach has been established, it will be important to evaluate effectiveness in the wider at-risk population, including rural regions, and to identify barriers to its implementation in those settings.

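### Baseline decision stage, on which the PDS tailors its messages, is adjusted for in the stage-change outcome but left to a change-in-coefficient check for FOBT uptake; it should be a fixed covariate there too

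*Protocol article*

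**What the plan says.** The PDS orders its messages by decision stage, "with the aim of moving people through stages of screening awareness and pre-screening contemplation to a decision to participate" (Background, on decision aid format). Table 2 lists PAPM stage in the Baseline Survey for all arms, with five stages from never having heard of FOBT to having decided to act.

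The Statistical analysis section treats the two primary outcomes differently.
- **Change in decision stage:** analysis of covariance, adjusted for baseline stage.
- **FOBT uptake:** a chi-squared test between arms, then log binomial models in which a change-in-coefficient method checks potential covariates and yields the final adjusted comparison. The examples are PHM factors, decisional conflict, gender, SES, age band and Internet access characteristics. The list is open-ended and does not name baseline stage.

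People reach the uptake comparison in two voluntary steps. They return an eligibility questionnaire, and those who "are eligible and willing to participate in the study will be randomly assigned to one of three arms". After randomisation, only those "who have not opted out of the trial at the BS phase and have completed a BS will receive" a kit. On numbers, "Randomisation of 3240 participants (1080 in each arm) takes into consideration predicted attrition of 50% at BS survey phase", which leaves 540 per arm, and "an initial sample of 18,000 needs to be approached, given our estimated attrition rates throughout the study". In the Discussion the authors write of the Internet restriction that "we do not consider this restriction will represent an undesirable degree of selection bias".

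**The concern.** Decision stage before the intervention is an obvious candidate predictor of returning a kit, and it is what the tailored arm acts on. A change-in-coefficient check is built to find confounders: it keeps a covariate only if adding it moves the arm coefficient. In a randomised comparison a strong predictor that happens to be balanced moves that coefficient little, so the check can discard it. Whether it stays then depends on chance imbalance and on the size of the observed effect, not on prognostic value.

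Two things are at stake. The adjusted uptake comparison may lose precision that the collected data would give. The uptake result may also go unconnected to the variable that drives the intervention, although the companion primary outcome is connected to it.

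**Working it through.** **Inputs from the protocol.** 18,000 approached, 3240 randomised, 50% lost at the Baseline Survey, 540 per arm offered a kit; 40% v 50%, 80% power, alpha 0.05 (Sample size considerations). National programme uptake is 39% (Background).

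**The plan's own figures.** 3240 × 0.5 = 1620, or 540 per arm. 3240/18,000 = 18% and 1620/18,000 = 9%. For 40% v 50% at two-sided 0.05, 80% power needs 388 per arm (408 with continuity correction). Power at 540 is 91%, so there is no shortfall on the plain reading. The 540 is nearly reproduced with alpha 0.05/3 and continuity correction (537), or with 90% power and continuity correction (538); the article states neither.

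**Assumptions.** No stage distribution is given. I take half of each arm as already decided to act, with uptake q = 70% to 90%, and 40% in the rest.

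**Would the check keep stage?** Chance imbalance in the decided share between two arms has SD √(2 × 0.5 × 0.5/540) = 0.0304. With q = 0.70, overall uptake is 0.55, so adjusting for stage moves the log risk ratio by an SD of about (0.70 − 0.40) × 0.0304/0.55 = 0.0166. The article gives no cut-off; I assume 10%, with 5% and 20% as the range.
- *Relative change in the coefficient, true log ratio ln(50/40) = 0.223.* A 10% rule needs a shift of 0.0223, or 1.34 SD: stage is kept in about 18% of trials. At 5% (0.0112, 0.67 SD) it is about 50%; at 20% (0.0446, 2.69 SD), under 1%.
- *Change in the risk ratio itself.* A 10% rule needs ln 1.10 = 0.0953, or 5.7 SD: practically never kept.
- *Smaller effect, 55% v 60%.* The log ratio is 0.087, the 10% cut-off 0.0087, or 0.52 SD: kept in about 60% of trials.

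So the check may drop stage, but need not.

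**What dropping it costs** (variance near no effect, adjusted relative to unadjusted):

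| q | Average within-stage variance / total variance | Log risk ratio, common across stages |
|---|---|---|
| 70% | 0.225/0.2475 = 0.91 | 330/405 = 0.81 |
| 80% | 0.20/0.24 = 0.83 | 405/630 = 0.64 |
| 90% | 0.165/0.2275 = 0.73 | 501/1305 = 0.38 |

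The second column applies to an estimate averaged over stages. The third uses information n·p/(2(1 − p)) per stage. At q = 70% that is 270 × 0.7/0.6 = 315 plus 270 × 0.4/1.2 = 90, total 405, against 540 × 0.55/0.9 = 330 unadjusted.

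**A limit of the adjusted model.** A single risk ratio gives the decided group 315/405 = 78% of the weight. If the effect were confined to the others, the adjusted log ratio would be near 90 × 0.223/405 = 0.050, against ln(60/55) = 0.087 unadjusted. The gain in the third column therefore needs a similar ratio across stages.

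**How informative would a stage-specific estimate be?** Assume 70–90% uptake in the decided group in every arm, and 40% v 50% in the rest, at two-sided 0.05:

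| Already decided | Power, all | Power, not yet decided |
|---|---|---|
| 25% | 69–70% | 82% (405 per arm) |
| 50% | 38–42% | 65% (270) |
| 75% | 13–17% | 38% (135) |

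The not-yet-decided group keeps 80% power only if it makes up at least 388/540 = 72% of survey completers.

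**The case against.** The covariate list is illustrative, so baseline stage can enter, and an article may leave the final model to a statistical analysis plan. That stands as far as the omission goes. What remains is the stated selection rule, which is a poor way to choose covariates in a randomised comparison wherever the list is completed.

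Randomisation balances stage among those randomised, whereas kits go only to Baseline Survey completers, who answer online in two arms and on paper in the third. If completion differs by arm, stage may be unbalanced and the check more likely to keep it. That is a further reason to fix it in advance. The survey precedes the tailored messages, so stage is a legitimate baseline variable.

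A reader might infer more: that the trial is enriched for people already willing to screen, that a null uptake result would be uninterpretable, and that the authors dismiss selection bias. The documents do not support this.
- Participants are willing to join the study, which is not the same as willing to screen. Enrichment is plausible but not shown.
- The Background says messages also reinforce favourable views, and it counts avoiding procrastination among the potential advantages of web delivery. People who have decided to act may still benefit.
- The 9% mixes ineligibility with refusal, so it is not an opt-in rate.
- The 40% is an example. Its closeness to 39% causes no shown loss of power: with the 10-point gap kept, power is 93% at 60% v 70% and 97% at 70% v 80%.
- The selection-bias remark concerns Internet access only, and the Discussion frames the trial as an efficacy study, with wider effectiveness deferred.
- Selection at the eligibility questionnaire precedes randomisation. It bears on generalisability and possible dilution, not on the internal validity of the comparison.

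**Conclusion.** The point holds as a modest improvement to the uptake analysis. Baseline stage is collected in every arm and used for one primary outcome, while for the other it depends on a rule that may discard it for reasons unrelated to its predictive value. Under the assumed half-decided split with 70% v 40% uptake, a 10% coefficient rule keeps it in about 18% of trials at a risk ratio of 1.25 and about 60% at 55% v 60%. Losing it forgoes 9% of the variance for a stage-averaged estimate, or 19% for a common log risk ratio; the loss is larger if stage predicts more strongly. All of this rests on an assumed stage distribution, assumed uptake by stage and an assumed cut-off. The chi-squared comparison is unaffected, and no bias or power shortfall is shown.

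**What to change.** In the Statistical analysis section, pre-specify baseline PAPM stage as a fixed covariate in the adjusted log binomial comparison of FOBT uptake, whatever the change-in-coefficient result, and report baseline stage by arm.

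An arm-by-stage estimate (decided to act v all earlier stages) may be added as exploratory support only, with its lower precision stated. It would also show whether one common risk ratio is a fair summary.

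Optionally, add to the Discussion that participants are also volunteers who returned the eligibility questionnaire and completed the Baseline Survey, without calling the 9% an opt-in rate.

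The cost is a few sentences, with no new data. Stage is known only for Baseline Survey completers, the same people who are sent kits, so the adjusted model applies to them. The analysts should also plan for log binomial fitting problems if uptake in the decided group is close to 100%.
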